***Randomisation procedure***

GP practices will be randomised in blocks using the balance algorithm for clustered randomised trials [41]. Baseline covariate data will include PCT, general practice list size and the Index of Multiple Deprivation. Practices that rapidly take up the offer of taking part in the study can form a first block, then those that take longer forming a second. The algorithm generates a set of allocations with the smallest imbalance statistic across the two arms. Final allocations will be randomly selected by the independent statistician on the Trial Steering Committee. This information will be passed to the PCRN who will be able to install the appropriate template into each practice and arrange for a GP Research Facilitator to meet with each practice.

***Post-randomisation***

Following randomisation a brief meeting will be held between the GP practice and a GP research facilitator from the PCRN. This will take place for all practices in both arms of the trial and will allow the template to be demonstrated and details of the recommended pathways of care to be disseminated. A laminated crib sheet with the full questions and response options, appropriate to each arm of the trial, will be placed in each consulting room in the GP practices. Details of the information that will be given to both arms is outlined below:

*Intervention arm*

In order to maximise “best practice” in addition to the screening template in the intervention arm, GPs will be referred to and advised to follow NICE recommendations for the holistic assessment and treatment of OA for all patients consulting with peripheral joint pain/OA [20]. GP’s will be recommended to refer to the appropriate NICE guidelines when a patient screens positively for anxiety and/or depression (further details below). A GP Research Facilitator will summarise these recommendations in a PowerPoint presentation and the following 4 papers will be disseminated to the practice (a copy of each paper will be provided for each consulting room):

- NICE clinical guideline 59: “Osteoarthritis. The care and management of osteoarthritis in adults” (quick reference guide) [20]
- NICE clinical guideline 91: “Depression in adults with a chronic physical health problem. Treatment and management” (quick reference guide) [11]
- British Medical Journal summary of new NICE guidelines: “Depression in adults, including those with a chronic physical health problem: summary of NICE guidance” by Pilling et al (2009) [21]
- NICE clinical guideline 113: “Generalised anxiety disorder and panic disorder (with or without agoraphobia) in adults. Management in primary, secondary and community care” (quick reference guide) [42]

Links to the websites where full length version of these guidelines will also be given to the GP practice.

For the case of depression, GP’s will be referred to the “Depression in adults with a chronic physical health problem” guidelines [11], which have a supporting article in the BMJ outlining how to put them into practice [21]. These guidelines suggest 4 steps to follow in the treatment of depression following a positive screen. In brief these are: 1) further questioning to establish the severity of depression; 2) persistent sub threshold depressive symptoms or mild-moderate depression: offering advice on sleep hygiene and actively monitoring depressive symptoms, depending on the severity of symptoms low-intensity psychological intervention or drug treatment may be warranted; 3) non response to initial treatment of severe depression: further treatment options and the possibility of collaborative care; and 4) for severe and complex depression or risk to life: high intensity interventions and medications.

GPs will be advised to follow the stepped care approach for generalised anxiety disorder as outlined in the quick reference clinical guidelines (“Generalised anxiety disorder and panic disorder (with or without agoraphobia) in adults. Management in primary, secondary and community care”) for the treatment of any patients who screen positive for anxiety symptoms [42]. These involve 4 steps: 1) identify, educate and actively monitor; 2) low-intensity psychological intervention; 3) high-intensity psychological intervention or drug treatment; 4) highly specialist treatment.

*Control arm*

In order to keep the control arm as close to “usual care” as possible, GP’s will be advised to follow their usual approach for responding to a patient’s pain intensity rating. Asking a patient the intensity of their pain is common practice in a primary care musculoskeletal pain consultation [20] and therefore should have little effect on the “usual care” that the GP provides. No additional information on OA best practice will be disseminated by the research team.

Having information on pain intensity at consultation in both arms of the trial will provide a further measurement to check that a balance between the intervention and control arms is achieved.

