## Primary objective

The primary objective of the trial is to determine whether screening for generalised anxiety and depressive symptoms in patients who consult their GP with OA or peripheral joint pain results in an improvement in their pain-related outcomes. Specifically, we hypothesise that patients who are screened for depressive and anxiety symptoms in their GP consultation will have an improvement in their self-reported current pain intensity and pain interference with daily activity ratings (numerical rating scale 0-10) over the 12 months following their consultation, compared to patients in the control arm. Growth curve models will be used to summarise the pattern of response over time between the groups. Changes in slope and intercept will reflect differences in rate of change and mean scores over the 12 months.

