***Cost-utility analysis***

The health economic analysis will determine the cost-utility of screening patients for anxiety and depression in OA compared with a standard consultation without screening. A cost-consequence analysis will initially be reported, describing all the important results relating to costs and consequences. Subsequently, an incremental cost-utility analysis will also be undertaken using patient responses to the EQ-5D questionnaire, to calculate the cost per additional QALY gained. The base case cost analysis will adopt a National Health Service (NHS) and personal social services (PSS) perspective [64]. A broader costing perspective will be considered in a sensitivity analysis, taking into account NHS/PSS costs, patients’ personal expenditure and costs associated with work loss. The data for costs is likely to have a skewed distribution therefore the plan is to explore the nature of the distribution of costs. If the data is not normally distributed, the non parametric comparison of means (e.g. bootstrapping) will be undertaken. Where differences in baseline characteristics occur between trial arms, for example in baseline EQ-5D score, the analysis will control for these baseline differences using regression-based adjustment. Efforts will be made to minimise the problem of missing data, but if this does pose a problem at the analysis stage then multiple imputation techniques will be used. The robustness of the results will be explored using sensitivity analysis. This will explore uncertainties in the trial based data itself, the methods employed to analyse the data and the generalisability of the results to other settings. Uncertainty in the confidence to be placed on the results of the economic analysis will be explored by estimating cost effectiveness acceptability curves. These plot the probability that the intervention is cost effective against threshold values for cost effectiveness.

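### The arms differ in osteoarthritis guideline dissemination as well as mood screening, but the objectives and the cost-utility question credit the effect to screening alone

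*Protocol*

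**What the plan says.** Post-randomisation, Intervention arm, opens its account of the extra material with "In order to maximise “best practice” in addition to the screening template in the intervention arm". It then states that "GPs will be referred to and advised to follow NICE recommendations for the holistic assessment and treatment of OA for all patients consulting"; the patients meant are those with peripheral joint pain or osteoarthritis. A facilitator summarises the recommendations in a presentation, and four papers go into every consulting room. One is the osteoarthritis guideline. The other three concern depression and anxiety, and GPs are pointed to the mood guidelines when a patient screens positive.

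Post-randomisation, Control arm, keeps GPs to their usual response to a pain rating and adds: "No additional information on OA best practice will be disseminated by the research team".

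The primary objective reads: "determine whether screening for generalised anxiety and depressive symptoms in patients who consult their GP with OA or peripheral joint pain results in an improvement"; the outcomes meant are pain-related. The secondary objective is the cost utility of screening. The Cost-utility analysis section sets out the "cost-utility of screening patients for anxiety and depression in OA compared with a standard consultation without screening".

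Two other places are broader. The Aims section describes a systems intervention to prompt holistic osteoarthritis treatment, compared with usual care. Methods/Design defines the systems intervention as the template plus the treatment approach the GP then follows.

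**The concern.** The question and the contrast do not match. The primary outcome is current pain intensity, which osteoarthritis treatment guidance is meant to affect. That guidance is directed at every intervention patient, including those who screen negative, and it does not depend on the template having been answered. A favourable difference could come from mood screening, from the osteoarthritis guidance, or from both. A weak or null screening effect could also be hidden by a helpful guidance effect.

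Reported in the words of the objectives, the result would be that screening for anxiety and depression improves pain and costs so much per QALY. That is a policy statement about screening which a two-arm comparison of packages cannot support.

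**Working it through.** **What each arm receives (Post-randomisation; Data collection)**

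| Component | Intervention | Control | Whom it targets |
|---|---|---|---|
| Pain rating on template | yes | yes | all |
| Two depression and two anxiety questions | yes | no | all intervention patients |
| Depression and anxiety guidelines | yes | no | screen-positive patients |
| Osteoarthritis guideline, slides, advice to follow it | yes | none from the research team | all intervention patients |

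The arm difference therefore estimates rows two to four together. The objectives name row two. Row three follows naturally from a positive screen and fits the Methods/Design definition. Row four is the separable addition.

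**Can the planned data separate them?** The Statistical analysis section describes only the comparison between arms. Control patients are not asked the mood questions at the consultation, so the template cannot identify control patients who would have screened positive or negative. The PHQ-8 and GAD-7 are first collected by post, after the consultation at which the intervention was delivered.

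**The plan's sample size, reproduced.** Inputs from Sample size: Δ = 0.2 SD, ρ = 0.5, n = 3, α = 0.05 (two-sided reproduces), power 0.90, icc 0.03, cluster size 30, 25% non-response.

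- M = 2(1.960 + 1.282)² × {1 + 2 × 0.5} / (3 × 0.2²) = 350.2; stated 350 per arm.
- Design effect = 1 + 29 × 0.03 = 1.87; 2 × 350 × 1.87 = 1309.
- 1309 / 30 = 43.6, so 44 practices; 1309 / 0.75 = 1745.

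The figures are right. The point does not dispute them.

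**Illustration of the misattribution.** The guidance effects here are assumptions; the documents give none. The time-averaged variance is (1 + 2 × 0.5)/3 = 2/3, with 350 effective patients per arm, so SE = √(2 × (2/3)/350) = 0.0617 SD. Suppose screening has no effect and guidance shifts mean pain by g:

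| g (SD) | g / SE | P(significant) = Φ(g/SE − 1.96) |
|---|---|---|
| 0.10 | 1.62 | 0.37 |
| 0.15 | 2.43 | 0.68 |
| 0.20 | 3.24 | 0.90 |

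**Reach of the two routes.** If the 0.2 SD average came only through screen-positive patients, each would need 0.2/p. The Background gives p = 0.182, but for depression alone on the PHQ-2, which yields 1.10 SD. In this trial a yes to any of four questions counts, so p should be higher. For an assumed 0.30 to 0.60 the requirement is 0.67 to 0.33 SD. Guidance is directed at all intervention patients and could give the same average with 0.2 SD each.

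**Is the split identifiable?** Write the arm difference as g + p × s, where s is the effect in screen-positive patients. With p = 0.5 and s = 0.4, screening accounts for all of 0.2 SD and g = 0. With s = 0, g = 0.2. The trial cannot tell these cases apart.

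**The case against.** The strongest reply is that a package was always intended. The Aims section speaks of a systems intervention for holistic osteoarthritis treatment, with mood recognition first, compared with usual care. Methods/Design says the recommended treatment course will be reinforced with intervention GPs. A pragmatic two-arm trial need not separate components, and on this reading screening in the objectives is shorthand. Much of this stands: the comparison with usual care is legitimate, and the randomised estimate of the package effect is not biased by bundling. It does not rescue the wording. The Aims section itself goes on to frame the question as routinely incorporating brief screening questions, and the three places that fix the hypothesis and the economic contrast name only screening.

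Second, the osteoarthritis guideline is published national guidance, and nothing stops control GPs from using it. The contrast is reinforcement against ordinary access. That may make the guidance effect small, but does not make it zero.

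A reader might go further and infer that most of any observed effect would be due to guidance. The documents do not support that: they contain no guidance effect and no effect in screen-positive patients, and the share can run from none to all.

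A reader might also infer a flat contradiction about control practices, because the general paragraph says the meeting held in both arms allows "details of the recommended pathways of care to be disseminated". That paragraph then refers on to arm-specific details, and the control text says usual care. This is loose drafting that needs reconciling, not proof that control GPs are shown the guideline.

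**Conclusion.** The point holds as a mismatch between the contrast and the claim. The trial will estimate the effect of the screening template plus osteoarthritis and mood guideline dissemination against a pain-rating template with usual care. It will not estimate the effect or the cost utility of screening alone, although the primary objective, secondary objective and cost-utility contrast say it will.

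It should not be read as a fault in the randomised comparison or the sample size. The size of any misattribution cannot be derived from the documents. The probabilities of 0.37, 0.68 and 0.90 show only that assumed guidance effects of 0.10 to 0.20 SD could produce a significant result with no screening effect. They rest on the protocol's own ρ, icc and cluster size, and on the assumed guidance effects.

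**What to change.** - Restate the primary objective and hypothesis, the secondary objective, the Cost-utility analysis contrast and the planned conclusion as: screening template plus osteoarthritis and mood guideline dissemination, versus pain-rating template with usual care. Make no claim about screening alone.
- In the cost-utility analysis, count the cost of delivering the guidance (presentation content and printed papers), since it is part of what is evaluated. Meetings take place in both arms, so the relevant quantity is the difference between them.
- Reconcile the general paragraph of Post-randomisation with its Control arm text, so that it is plain what control practices are shown.

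This needs no new data and leaves 1309 patients and 44 practices unchanged. The downside is a less specific claim.

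Withdrawing the osteoarthritis guideline from the intervention pack is not recommended. The Timeline in the substudy amendment reports templates being switched off at the 8 practices in block 1, with 5 in block 2 active. A change now would give early and late practices different interventions, and the Run-in period section excludes run-in data if substantial amendments are needed. Separating the components with a third arm of 350 per arm before clustering would take 3 × 350 × 1.87 = 1963.5, about 1964 patients, and 1963.5/30 = 65.5, so 66 practices. Rewording is the proportionate remedy.

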***Activation of the screening template***

Potentially eligible participants will be identified by their GP in the consultation. When the GP enters a peripheral joint pain or OA Read code (from the pre-determined study list) into the electronic patient record then the electronic screening template will be automatically activated. This will only occur for the first time such a Read code is entered for a patient during the study period, ensuring that each patient can only be sampled once. At this stage GPs will apply the exclusion criteria. Activation of the main template will prompt the GP to ask the patient the questions on the template and to record their answers. The consultation will then continue as the GP sees fit; however, details of how to respond to a positive screen for depression and/or anxiety will be reinforced in a post-randomisation meeting (as described above).

During the consultation the GP will provide patients with a short information postcard introducing the study; this is so patients are not surprised when contacted by the research team at later date.

***Informed consent***

In cluster randomised trials participants are usually not asked for their consent to randomisation [43], since cluster randomisation usually occurs before individual participants can be identified [39]. It is accepted in cluster randomised trials that a “guardian” [44] or “gate-keeper” [45] for the cluster provides consent for the individuals in their care to be entered into the trial. In this trial consent will be taken from each GP practice to say that as “guardians” for the patients in their care, they are willing to both enter the trial and to be randomised into either arm of the trial. In cluster randomised trials such as this one, where it would not be feasible to gain individual consent prior to randomisation, it is acceptable to gain individual consent post-randomisation for entry into the study and for follow-up. In this trial participants will be asked to consent to completing postal questionnaires and for their medical records to be accessed. Both control and intervention arms will be given the same information about the trial and although they will not be explicitly informed about the intervention (that has already taken place) selection bias and contamination bias will be reduced [39].

***Mailing procedure***

An illustrated summary of the mailing procedure is provided in Figure 2. All eligible patients will be sent a study pack as outlined above. Those who do not respond within 2 weeks will be contacted again with a postcard reminder. At 4 weeks those who have not responded will be sent a second study pack and reminder letter. At baseline, patients who have still not responded at 8 weeks will be recorded as non-responders and will not be contacted again at any point in the study and their medical records will not be accessed. Participants who respond to the questionnaire but who do not consent to further contact, which will be specified on the consent form as being in 3, 6 and 12 months time, will also be recorded in the database as a non-consenting responder, ensuring that we do not contact them again in the future (this may occur by returning a completed or blank questionnaire or verbally by telephone conversation).

*Follow-up*

Participants who return a questionnaire and consent to participate at baseline will be sent a follow-up questionnaire at 3, 6 and 12 months following their index consultation. In order to maximise participation a short questionnaire, including only minimal data collection items (outlined below), will be sent to participants who have not responded to the full postal questionnaire at 6 weeks. At 6 and 12 month follow-up points an additional telephone call will be used at 8 weeks (for those participants who provided a telephone number in their baseline questionnaire) to attempt to contact non-responders in order to get information on their pain intensity at that time. Three telephone call attempts will be made to contact each participant. The mailing procedure is outline in Figure 2.

**Figure 2:** Mailing procedure

[figure not shown]

***Data collection***

Data collection will take three forms: screening template in the GP consultation, postal questionnaire and medical record review.

1. *Electronic screening template*

The screening template consists of five and one question(s) for the intervention and control arms, respectively. The content for both arms is summarised in Table 1. Appendix 1 gives full details of the screening template for both arms of the trial, including the response options. All responses will be recorded on the pop-up template during the consultation.

*Intervention arm*

In order to screen for depression two items previously validated in primary care populations [12] will be used. These questions are adapted from the PHQ-2 [46] and are routinely used as part of the General Practice Contract for patients with CHD and diabetes and are also recommended by the recent guidelines for comorbid depression with a chronic physical health problem [11]. Anxiety will be screened for using two items adapted from the GAD-2 [26]. Both the PHQ-2 and GAD-2 have been shown to be reliable and valid ultra-short screening tools for depression and anxiety in a general population setting [47]. In both instances the adaptations from the original 2-item depression and anxiety tools refers to a simplified response of “yes” or “no” to having experienced such symptoms in the past month. The intervention arm will also be asked to rate their current pain on a numerical rating scale from 0 (“no pain”) to 10 (“pain as bad as it could be”). Patients will be considered as having screened positive for depression if they answer “yes” to either of the two depression questions. Similarly, answering “yes” to at least 1 of the 2 anxiety questions will result in a positive screen for anxiety.

*Control arm*

The template for the control arm will prompt GPs to ask patients to rate their current pain on a numerical rating scale from 0 (“no pain”) to 10 (“pain as bad as it could be”). A question typical of those routinely asked in an OA consultation.

**Table 1:** Summary of screening template content

|  | **Conceptual domain** | **Operational definition** | **Empirical measure** | **Number of items** |
| --- | --- | --- | --- | --- |
| **Intervention arm** | Pain intensity | Current pain intensity (of the index pain, at the time of the index consultation) | 0-10 NRS (48) | 1 |
|  | Depression | Low mood, anhedonia in the past month | Depression screening question for primary care (12) | 2 |
|  | Anxiety | Nervousness and worrying in the past month | Modified GAD-2 (26) | 2 |
| **Control Arm** | Pain intensity | Current pain intensity (of the index pain, at the time of the index consultation) | 0-10 NRS (48) | 1 |
| NRS – numerical rating scale | | | | |

*2a. Full postal Questionnaire*

The postal questionnaires are designed to collect information on descriptive characteristics of the participants, in-depth depression and anxiety measures, pain-related characteristics and detailed data collection of our outcome measures. The items to be included in each of the four postal questionnaires (baseline, 3, 6 and 12 months) are summarised in Table 2. Further details of the outcome measures of interest are provided below.

*Outcome measures*

1. *Primary outcomes*

The primary outcome measure of the study will be index pain severity across the study time period. The Chronic Pain Grade [48] will be included in each of the postal questionnaires, this includes the question “How would you rate your pain on a 0-10 scale at the **present time** where 0 is “no pain” and 10 is “pain as bad as it could be”?”. This question is also part of the consultation screening template for both arms of the study.

1. *Secondary outcomes*

Pain interference with daily activities will be assessed on a numerical rating scale of 0-10. The numerical rating scales for pain intensity and pain interference form part of the Chronic Pain Grade [48], a 7-item scale from which composite pain intensity and interference scores will be generated. A further secondary outcome measure is global function, as assessed by the SF-12 [49]. Physical function relating specifically to knee and/or hip pain will be assessed using the short form WOMAC function subscale (8 items) and two stem questions to determine which participants have knee and/or hip pain [50]. Detailed assessment of depressive and anxiety symptoms will be collected using the PHQ-8 and GAD-7, respectively. The PHQ-8 is derived from the PHQ-9; a validated 9-item measure of depression designed to both diagnose and assess the severity of depression [51,52]. The GAD-7 was established using both DSM-IV criteria for general anxiety disorder and items from previous existing anxiety scales [53]. As with the PHQ-8, the GAD-7 enquires about symptoms experienced over the last two weeks. The first two items on the PHQ-9 and GAD-7 comprise the PHQ-2 and GAD-2, respectively, which are used to screen for depressive and anxiety symptoms in the intervention arm of this trial. Additional items will be included in the questionnaire to gather further information about participants’ index pain symptoms, other sites of pain, pain catastrophising scale [54], general medical health (including comorbidities and medication use) and demographic details.

1. *Health economics outcomes*

Costs: Health sector costs will include primary and secondary care contacts, investigations, medication and contacts with other health care professionals such as physiotherapists and community psychiatric nurses. Primary health care resource use (GP and practice nurse consultations/home visits) and medications will be collected from a review of primary care medical records, covering the full 12 month follow-up period for all study participants. Information on secondary care attendances and patient borne costs will be gathered using the postal self-report questionnaires. Questions on patients’ personal expenditure will concentrate on private health care use and over-the-counter treatments. Productivity costs will be calculated using data collected on occupation and days off work due to illness. Unit costs will be obtained from standard sources and health care providers. Due to the nature of the study, generic health care resource use will be collected (i.e. not specific to the treatment of OA). Information on resource use from the self-report questionnaires will be collected at 6 months and 12 months, with each questionnaire covering a 6 month recall period.

Quality of life measures: All patients will be asked to complete the 5-level version of the EuroQoL-5D (EQ-5D) [55] questionnaire at baseline, 3 months, 6 month and 12 months in order that quality-adjusted life years (QALYs) over the 12 month time period can be calculated for each study participant. The QALYs combine information on health-related quality of life and survival. The SF-12 will also be included as a measure of generic health-related quality of life, thus allowing an alternative method of calculating QALYs using the SF-6D in a sensitivity analysis.

The conceptual domains, operational definitions and empirical measures of each of the items included in the postal questionnaires are detailed in Table 2. This table also highlights in which of the questionnaires (baseline, 3, 6 or 12 months) the item is included.

**Table 2:** Summary of full postal questionnaire content

| **Conceptual domain** | **Operational definition** | **Empirical measure** | **Number of items** | **Time** |
| --- | --- | --- | --- | --- |
| **Primary Outcomes** |  |  |  |  |
| Pain intensity | Current intensity of the index pain | NRS 0-10 * | 1 | B, 3FU, 6FU, 12FU |
| **Secondary Outcomes** | |  |  |  |
| Disability | Composite characteristic pain interference with daily activities, recreation and work during the past 3 months. | Number of days (1 item) and NRS 0-10 (3 items provide composite disability score of 0-100)* | 4 | B, 3FU, 6FU, 12FU |
| Characteristic pain intensity | Composite current and past and average pain intensity during the past 3 months. | NRS 0-10 (3 items provide a composite characteristic pain intensity score of 0-100)* | 3 | B, 3FU, 6FU, 12FU |
| Index pain location | Site of index pain complaint | Choice of anatomical site | 1 | B |
| Nature of onset | Traumatic onset | Yes / no / unsure | 1 | B |
| Episode duration | Time since last whole month free from this pain | Episode duration (56) | 1 | B, 3FU. 6FU, 12FU |
| Days in pain | Days in past 6 months with index pain | No days / 1-30 days / 31-89 days / 90+ days | 1 | B, 6FU, 12FU |
| Multiple site / chronic widespread pain | Pain in sites other than the index site over the last month. Manchester definition of widespread pain; Keele definition of number of pain sites; chronicity of pain; pain in the knee or hip | Yes/no; Body manikin (57,58) | 4 | B, 3FU, 6FU, 12FU |
| Pain consultation | First consultation for this pain complaint | Yes / no | 1 | B |
| Pain improvement | Improvement in pain at index pain site | 6 point Likert scale | 1 | 3FU, 6FU, 12FU |
| Further pain consultation | Consulted since index consultation with the same pain site | Yes / no | 1 | 3FU, 6FU, 12FU |
| Satisfaction with consultation | Satisfaction with questions asked during consultation | Yes/no/unsure; details; list of items asked | 4 | B |
| Physical function related to knee and/or hip pain | Degree of difficulty with 8 daily activities | Short form WOMAC function subscale (50) | 8 | B, 3FU, 6FU, 12FU |
| Catastrophic coping | Catastrophic coping relating to index pain | Pain catastrophising scale (54) | 9 | B |
| Anxiety | Generalised anxiety symptoms in past 2 weeks | GAD-7 (53) | 7 | B, 3FU, 6FU, 12FU |
| Depression | Depressive symptoms in past 2 weeks | PHQ-8 (59) | 8 | B, 3FU, 6FU 12FU |
| Discussion of mood in consultation | Did doctor ask about mood during index consultation | Yes / no / unsure | 1 | B |
| Diagnosis of depression | Ever diagnosed by doctor as depressed | Yes / no / unsure | 1 | B |
| Diagnosis of anxiety | Ever diagnosed by doctor with an anxiety disorder | Yes / no / unsure | 1 | B |
| **Quality of life measures** | |  |  |  |
| General health | Mental and physical well-being | SF-12 (49) | 12 | B, 3FU, 6FU 12FU |
| General health | Utility-based quality of life | EuroQol-5D (55) | 5 | B, 3FU, 6FU 12FU |
| Comorbidities | Ever been diagnosed with any from a list of possible comorbidities | Yes |  | B |
| Fractures | Ever fractured hip/wrist/other bones |  |  | B |
| Falls | Falls in the past 12 months | Yes/No | 1 | B |
| **Healthcare costs** |  |  |  |  |
| Medication usage | Select from list of analgesic and psychiatric medicines that currently taking |  |  | B |
| Health care resource use | Use of non-primary care health care resources | Yes/No and details of resource use if Yes | 3 | B, 6FU, 12FU |
| OTC medication | OTC medication expenditure | Details of OTC medications |  | 6FU, 12FU |
| **Miscellaneous** |  |  |  |  |
| Age | Age at index consultation | Date of birth | 1 | B, 3FU, 6FU, 12FU |
| Sex | Sex | Male / Female | 1 | B, 3FU, 6FU, 12FU |
| Employment status and absence from work | Employment status at time of questionnaire and days of work absence | Yes/No and details | 10 | B, 6FU, 12FU |
| Socioeconomic status | Occupational class based on individual (i) current or (ii) most recent job title | Job title – categorised as manual / non-manual (60,61) | 2 | B |
| Living arrangement | Live alone | Yes / No | 1 | B |
| Marital status | Marital status at time of Baseline Questionnaire | Married / Single / Divorced / Widowed / Separated / Cohabiting | 1 | B |
| Social support | Availability of instrumental and emotional support (yes/no/no need) | Single items (62) | 2 | B, 6 FU, 12 FU |
| Obesity | Body Mass Index | Height (m / ft, in), weight (kg / st, lb) | 2 | B |
| B – baseline; FU – follow-up (in months); OTC – over the counter; NRS – numerical rating scale; * 7 items form the Chronic Pain Grade (48). | | | | |

*2b. Short postal questionnaire*

This questionnaire will contain a minimum set of data that we are interested in, namely: Chronic Pain Grade and EQ-5D (summarised in Table 3).

**Table 3:** Summary of short postal questionnaire content

| **Conceptual domain** | **Operational definition** | **Empirical measure** | **Number of items** | **Time** |
| --- | --- | --- | --- | --- |
| Index global severity | Composite characteristic pain intensity, interference with activities, and disability days (of the index pain, in the month preceding index consultation) | Chronic Pain Grade (48)* | 7 | 3FU, 6FU, 12FU |
| General health | Utility-based quality of life | EuroQol-5D (55) | 5 | 3FU, 6FU 12FU |
| Age | Age at index consultation | Date of birth | 1 | 3FU, 6FU, 12FU |
| Sex | Sex | Male / Female | 1 | 3FU, 6FU, 12FU |
| FU – follow-up (in months); * Chronic pain grade includes primary outcome measure of current pain intensity | | | | |

*2c. Telephone questionnaire*

At each of the 6 and 12 month follow-up timepoints we will attempt to contact by telephone participants who do not respond to either the full or short questionnaires. Participants will be asked the brief questions regarding the intensity of the pain in their index pain site and how much this interferes with their daily activities. They will be asked to rate these on a numerical rating scale of 0-10 (summarised in Table 4).

**Table 4:** Summary of telephone questionnaire content

| **Conceptual domain** | **Operational definition** | **Empirical measure** | **Number of items** | **Time** |
| --- | --- | --- | --- | --- |
| Pain intensity and interference | Pain intensity and interference with activities | NRS (0-10) | 2 | 6FU, 12FU |
| Age | Age at index consultation | Date of birth | 1 | 6FU, 12FU |
| FU – follow-up (in months); NRS – numerical rating scale | | | | |

1. *Medical record review*

A medical record review will take place for all participants who have given their consent (at the time of the baseline questionnaire) to have their medical records reviewed (summarised in Table 5). This will allow us to download their data from the consultation screening template. Date of consultation, general practice and index Read code information will also be collected at this time. After the 12 month follow-up period a more detailed review will be carried out to enable us to assess prescriptions, referrals for further treatment, and number of consultations and whether these are for OA or mood problems. It will also allow us to determine whether there had been any previous diagnosis or treatment for depressive or anxiety symptoms. This data will provide primary health care resource use for the health economic analysis. The information collected on the treatment paths taken for patients who have a completed template will be fed back to practices following the 12 month record review, allowing practices in the intervention arm to see how closely they have followed recommended NICE guidelines. This information will also be of interest to GP practices in the control arm.

**Table 5:** Summary of medical record review

| Item | **Time** |
| --- | --- |
| Content of screening template | B |
| Prescriptions | 12FU |
| Referrals | 12FU |
| Number of OA / mood problems consultations | 12FU |
| B – baseline; FU – follow-up (in months) | |

